## Abstract

**Background:**

Polycystic ovary syndrome (PCOS) is the most common heterogeneous endocrine disease among women of childbearing age, characterized by androgen excess and ovarian dysfunction. Aerobic exercise is an important solution used to manage PCOS, due to its multiple benefits. *Yi Jin Jing* is an important component of traditional Chinese exercise (TCE), based on the root of traditional Chinese medicine theory (TCM), which focuses on keeping the body as a whole in a harmonious state. However, to date there is no literature on the benign effects of *Yi Jin Jing* on PCOS. The primary purpose of this protocol is to assess the effectiveness of aerobic exercise versus *Yi Jin Jing*, on the management of ovarian function in young overweight/obese women with PCOS.

**Methods:**

The study will conduct a controlled randomized, superiority trial with three-arm parallel groups, recruiting 90 women diagnosed with PCOS, ages between 18 and 35 years, with a body mass index (BMI) ≥ 23 kg/m^2^. Women will be randomly assigned to either control group (combined oral contraceptives) or one of the intervention groups (*Yi Jin Jing* group or aerobic exercise group) with an allocation rate of 1:1:1. After randomization, the intervention will be conducted within a 12-week period. The primary outcome would be anti-Mullerian hormone (AMH) level; the secondary outcomes would be biochemical profiles, ovarian volume, antral follicle count, BMI, menstrual frequency, and homeostasis model assessment of insulin resistance (HOMA-IR). Outcome measures would be collected during baseline and end of treatment. Reporting of the study will follow the Standard Protocol Items: Recommendations for Interventional Trials (SPIRIT) statement.

**Discussion:**

This proposed study will be the first randomized clinical trial to evaluate the comparative effectiveness of aerobic exercise versus *Yi Jin Jing* on the management of ovarian function in young overweight/obese women with PCOS. The results may provide a new evidence-based management strategy for young women with PCOS.

**Trial registration:**

Chinese Clinical Trial Registry ChiCTR1900022385. Registered on 9 April 2019

**Supplementary Information:**

The online version contains supplementary material available at 10.1186/s13063-022-06377-8.

## Background

Polycystic ovary syndrome (PCOS) is the foremost endocrinopathy which affects 6–10% of the reproductive stages in women [1]. PCOS is characterized by androgen excess and ovarian dysfunction [2] and is further aggravated by hyperinsulinemia [3], thus causing a number of reproductive and metabolic dysfunctions. The main clinical features include anovulation, menstrual irregularity, infertility, acne, and metabolic disorders [2, 4, 5], affecting diagnosed limiting women lifespan [6] and reducing health-related quality of life. Presenting signs and symptoms are heterogeneous and could change with aging; reproductive function disorders are the primary disturbances in younger women with PCOS [7–9]. About 60% PCOS women are overweight or obese [10], and excess weight could significantly worsen reproductive features for PCOS [11], as well as weakening the effectiveness of fertility treatment and increasing the risk of pregnancy complications [12]. In 2005, the annual cost on reproductive-aged PCOS women in the USA was up to $4.36 billion [13], resulting in a tremendous economic burden to families and the society as a whole. Thus, improving ovarian function is crucial for young overweight/obese women with PCOS.

Lifestyle modification (diet and exercise) is recommended as the first-line management for PCOS to achieve effective weight management and to optimize hormonal profiles, ultimately improving quality of life [14, 15]. In relation to diet, exercise has equal and sustainable effect in maintenance of weight loss, improvement of menstrual status, and ovulation in overweight/obese women with PCOS [16]. While dietary program is at the expense of muscle mass [16], exercise could reduce more fat mass, retain lean muscle mass, and improve body composition [17, 18], suggesting the optimal role exercise plays in lifestyle management for PCOS. Al-Eisa et al. [19] found that 12-week aerobic training can significantly improve reproductive function by decreasing body mass index (BMI), anti-Mullerian hormone (AMH), and antral follicle count in PCOS group, while increasing follicle-stimulating hormone (FSH) and estradiol (E_2_). Aerobic exercise could significantly reduce the number of follicles developments between 2 and 9 mm and improve ovarian morphology [20]. Aerobic exercise could improve quality of life of women with PCOS [21]. An updated meta-analysis consisting of 18 studies, with total of 1978 participants showed that exercise intervention may improve pregnancy rates in women with reproductive health problems [22]. However, another recent meta-analysis including 14 studies which evaluated a total of 617 women with PCOS pointed out that the impact of exercise interventions on ovarian function remains ambiguous, without sufficient evidence to quantify the effect of exercise on ovulation quantitatively of affected women [23]. The conflicting evidence suggests the need for further studies on the effect of exercise intervention on ovarian function of women with PCOS.

According to traditional Chinese medicine (TCM) theory, kidney deficiency is viewed as the root problem in PCOS [24], kidney dominates the function of “kidney-Tian Gui-Chong Ren-uterus axis” [24]. The dysfunction of hypothalamic-pituitary-ovary (HPO) axis plays a role on pathogenesis of PCOS, resulting in increased gonadotrophin releasing hormone and luteinizing hormone (LH), then impacting ovarian androgen synthesis and folliculogenesis [2]. The “kidney-Tian Gui-Chong Ren-uterus” axis of TCM is similar to HPO axis in modern medicine [25]. Where the function of the kidney resembles  that of the hypothalamus [24], the function of *Tian Gui* resembles that of the sex hormone [26], and the function of *Chong* meridian and *Ren* meridian resemble that of the pituitary gonadotropin [24]. Thus, the kidney deficiency could lead to disturbance of *Tian Gui* [27] and disharmony of *Chong* and *Ren* meridians [26].

Furthermore, overweight/obese PCOS women are closely related to phlegm-dampness constitution [28, 29]; phlegm-dampness could block meridians and causes Qi stagnation and blood stasis, aggerating a number of reproductive dysfunctions.

*Yi Jin Jing*, which dates back to ancient China, consists of soft and stretching body movements, breath control, and meditation [30]. Practicing *Yi Jin Jing* could achieve harmonious integration of body and mind, by attaining a relaxed and deep focused state. *Yi Jin Jing*, as an important part of traditional Chinese exercise (TCE), has a theoretical root on TCM, having a dual nature of exercise and medical treatment [31]. *Yi Jin Jing* training emphasis on waist movement thus could strengthen the kidney through waist movement exercises, and the waist is termed as “the house of kidney” from the TCM theory [31]. *Yi Jin Jing* could also stimulate the *Chong* and *Ren* meridians through flexion and extension movements, balancing of the Yin and Yang, and harmonizing Qi [31, 32] to attain the holism and benign effects.

Hong et al. [33] discovered that *Yi Jin Jing* may balance level of estrogen and progesterone, reduce the level of prostaglandins PGF2a, and improve primary dysmenorrhea symptoms, while Chen et al. [34] found that 3 months of *Yi Jin Jing* training could improve sex hormones levels of FSH, LH, and testosterone (T) and reduce the proportion of E_2_/T in elderly men, hinting the benign role of *Yi Jin Jing* on reproductive health. *Yi Jin Jing* could reduce BMI and fat mass and improve lean muscle [35], helping to improve phlegm-dampness constitution. In conclusion, *Yi Jin Jing* could be used to manage PCOS-related symptom by addressing both manifestation (phlegm-dampness) and root cause (kidney deficiency). To our knowledge, no studies investigating the effect of *Yi Jin Jing* in women with PCOS have been conducted. Therefore, we intend to see the effect of *Yi Jin Jing* in PCOS and comparative effectiveness of aerobic exercise versus *Yi Jin Jing* on the reproductive health in young overweight/obese women with PCOS, proving evidence-based solution for feasibility and executing a new convenient mean for managing PCOS.

## Methods/design

### Objectives

The main objective of this study is to evaluate the comparative effectiveness of aerobic exercise versus *Yi Jin Jing* on ovarian function in young overweight/obese women with PCOS.

### Study design

The study is designed as a controlled randomized, superiority trial with three-arm parallel groups. Reporting of the study will follow the Standard Protocol Items: Recommendations for Interventional Trials (SPIRIT) statement (Additional file 1). A total number of 90 diagnosed PCOS patients will be recruited from Yue yang Integrated Chinese and Western Medicine Hospital, Affiliated to Shanghai University of Traditional Chinese Medicine. Patients will be recruited from the gynecologist ward through fliers, posters, and gynecologist recommendations. Patients will be randomly assigned to two intervention and control group with an allocation ratio of 1:1:1. After randomization, the intervention groups will undergo either *Yi Jin Jing* or aerobic exercise training for 12 consecutive weeks and the control group with no training intervention but take oral contraceptives (OCPs). Post-test measurements will be conducted based on the primary and secondary outcomes in comparison to the baseline measures.

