#### Sample size

AMH is the target effect, according to a similar research by Moran [47], where the mean AMH level before intervention was 59.1pmoL/L, standard deviation was 20.5pmoL/L, and AMH declined by 13.2pmoL/L in response to exercise. We require 25 participants per group to achieve a power of 80%, two-sided *α* = 0.05. With an approximate attrition rate of 20%, we will recruit 90 participants in total with 30 participants per group.

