### Statistical methods

The intention-to-treat principle will be used in the statistical analysis. We will use multiple imputation, based on 5 replications and a chained equation approach method in the R MI procedure, to account for missing data. Continuous variables will be presented by mean ± standard deviation. We will use the Kolmogorov–Smirnov test to see the normality and Levene test to see homogeneity of variance. Data transformations, such as logarithmic transformation or arcsine square root transformation, will be applied in cases of a non-normal distribution. Analysis of variance (ANOVA) will be used for comparing the differences between groups, and Bonferroni test will be applied if the difference is found to be significant. Paired *t*-test will be used for comparing the differences within groups. Differences between groups of the categorical data (menstrual frequency) will be compared by Kruskal–Wallis test, and Nemenyi test will be applied if the difference is found to be significant. A two-sided *P* value less than 0.05 will be considered significant.

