## Discussion

Existing pharmaceutical agents such as OCPs have been associated with side effects, and OCPs may potentially have an adverse cardiovascular risk, elevated inflammatory markers, and decreased insulin sensitivity [48]. Non-pharmacological interventions, such as aerobic exercise and *Yi Jin Jing*, have limited side effects and are widely applicable. *Yi Jin Jing* is a pleasant mind–body exercise, which is similar to other TCEs, such as Tai Chi, which has mild intensity [49]. We hypothesize that *Yi Jin Jing* and aerobic exercise could decrease AMH level and improve menstrual pattern as well as other secondary outcomes compared to control group, thus improving ovarian function of young overweight/obese women with PCOS. Obesity, insulin resistance, and metabolic disturbances are predominant in older women with PCOS; the early management of younger PCOS women might reduce their risk of insulin resistance and metabolic disturbances later in life [7]. As a result, *Yi Jin Jing* may offer an easy and inexpensive alternative management for younger women with PCOS, to further avoid long-term complications.

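### The main objective compares aerobic exercise with Yi Jin Jing, but the superiority test that is planned cannot show that the two are similar; the difference and its confidence interval should carry the conclusion

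*Protocol article*

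**What the plan says.** All references are to the protocol article.

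- **Objectives:** "The main objective of this study is to evaluate the comparative effectiveness of aerobic exercise versus" Yi Jin Jing. The Abstract states the same primary purpose.
- **Study design:** "The study is designed as a controlled randomized, superiority trial with three-arm parallel groups". The label covers the whole trial and is not tied to a particular pair of arms.
- **Discussion:** the stated hypothesis is that Yi Jin Jing and "aerobic exercise could decrease AMH level and improve menstrual pattern as well as other secondary outcomes compared to control group". Both exercises are expected to beat control. No direction, size or margin is given for one exercise against the other.
- **Statistical methods:** the three groups are compared by ANOVA, and a "Bonferroni test will be applied if the difference is found to be significant". The threshold is a two-sided P "value less than 0.05 will be considered significant".
- **Sample size:** the effect comes from a similar study in which the "standard deviation was 20.5pmoL/L, and AMH declined by 13.2pmoL/L in response to exercise". This is a decline after exercise, not a gap between two kinds of exercise. The stated requirement is 25 per group for 80% power, raised to 30 for attrition.

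**The concern.** The type of hypothesis does not match the main question. The superiority label and the only stated hypothesis fit exercise against contraceptive. The main objective is exercise against exercise, and there the plan expects both arms to improve and predicts no winner.

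For that contrast the plan fixes a gate (the ANOVA) and a threshold (P < 0.05). If the exercises have similar effects, the trial will usually end in one of two ways: the ANOVA is not significant and the pair is never compared, or the pair is compared and the result is not significant. Either could easily be written up as no difference between the exercises. At this sample size such a result is nearly as probable when one exercise is half as effective as when the two are equal, so the main objective could be reported as met on data that do not settle it.

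**Working it through.** **Inputs.** SD 20.5 pmol/L (AMH before intervention), effect 13.2 pmol/L, 25 per group, 80% power and two-sided 0.05, all from Sample size; ANOVA followed by Bonferroni, from Statistical methods. Assumptions: 20.5 is the SD of the analysed value, 13.2 stands for the whole exercise effect, and there is no baseline adjustment unless stated.

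**The plan's own figure.** For two independent means, n = 2 × [20.5 × (1.960 + 0.842) / 13.2]² = 37.9, so 38 per group (39 by the t-test). The stated 25 does not follow from these inputs for a between-group comparison; power at 25 is about 61%. A figure of 25 does appear if a baseline-adjusted analysis with an unstated correlation of 0.6 is assumed. I use 25 below because it is the plan's figure.

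**Precision of aerobic minus Yi Jin Jing.**

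- SE = 20.5 × √(2/25) = 5.80 pmol/L.
- 95% half-width = 2.011 × 5.80 = 11.7 pmol/L, and 11.7 / 13.2 = 88% of the assumed effect.
- With 30 per arm the half-width is 10.6 pmol/L (80%).
- With baseline adjustment at 25 per arm, SD = 20.5 × √(1 − r²): 10.1 pmol/L at an assumed r = 0.5 and 8.3 pmol/L at r = 0.7.
- Gap detectable with 80% power: (1.960 + 0.842) × 5.80 = 16.2 pmol/L, more than the whole assumed effect.

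**Chance of a non-significant pairwise result** (noncentral t, 25 per arm, before the ANOVA gate):

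| True gap between exercises (pmol/L) | At 0.05 | At 0.05/3 = 0.0167 |
|---|---|---|
| 0 (equal) | 95% | 98% |
| 3.3 | 91% | 97% |
| 6.6 (one has half the effect) | 80% | 90% |
| 13.2 (one has no effect) | 39% | 57% |

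How well does a non-significant result separate equal from half as effective? The ratio of the two probabilities is 0.950 / 0.800 = 1.19 at 0.05, and 0.983 / 0.901 = 1.09 at the planned Bonferroni level. A ratio of 1 would mean no information.

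**The ANOVA gate.** Suppose 13.2 is also the advantage over control, which is uncertain because control is an active drug. If both exercises achieve 13.2, the ANOVA is significant in 63% of trials at 25 per arm, so 37% would never reach the pairwise step. If one achieves 13.2 and the other 6.6, the ANOVA is significant in 50%.

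**What an interval rule would do.** Take an illustrative margin of 6.6 pmol/L (half of 13.2). If the exercises are equal, the chance that the 95% interval excludes a loss that large is Φ(6.6/5.80 − 1.960) = Φ(−0.82), about 21%. For 80% power this margin would need 152 per group.

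**The case against.** **The label fits the hypothesis.** The only stated hypothesis is that each exercise beats control, and that is a superiority hypothesis. A two-sided test is also a normal way to ask whether two treatments differ. This stands for the comparisons with control. It does not help the main objective, for which a non-significant difference test cannot be read as similarity.

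**Expecting both to work is not expecting equality.** This stands. The plan assumes no gap, zero or otherwise, so a reader might infer that non-significance is the predicted result, and the documents do not say so. At a gap of 13.2 the unadjusted test would be significant in about 61% of trials. That gap would mean that one exercise has no effect, against the plan's own hypothesis.

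**The confidence interval may be in the SAP.** This is fair. An article need not list every output, and the interval can be computed from arm means, SDs and numbers. The point therefore rests on what is fixed: the label, the gate and the threshold. Nor is it right that a non-significant result tells nothing, since an interval would still rule out very large differences.

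**The claim of an alternative.** A reader might infer that the authors plan to present Yi Jin Jing as a substitute for aerobic exercise, because the Discussion says that it "may offer an easy and inexpensive alternative management for younger women with PCOS". The text does not support that. The sentence is tentative, and its paragraph opens with the drawbacks of oral contraceptives. It can be read as an alternative to the drug, which superiority over control would support. The sentence is not an error.

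**A margin would seldom be met.** This also stands: about 21% for 6.6 pmol/L. It is a reason to expect an inconclusive comparison, not a reason to let P ≥ 0.05 stand in for similarity.

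**Conclusion.** The concern holds for the exercise-against-exercise contrast. Followed as written, the plan may give its main objective no pairwise result, or a non-significant one that barely separates equal effectiveness from half: 95% against 80% at 0.05, and 98% against 90% at 0.0167. The interval would be about ±11.7 pmol/L, against an assumed effect of 13.2.

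These figures rest on SD 20.5, 25 evaluable per arm, no baseline adjustment, and 13.2 as a stand-in for the full effect although it is a within-group decline. Adjustment at an assumed correlation of 0.5 to 0.7 narrows the interval to between ±10.1 and ±8.3 pmol/L, still 77% to 63% of 13.2, so the conclusion does not change.

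The verdict does not extend to the comparisons with control, where a superiority framework is consistent with the stated hypothesis.

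**What to change.** 1. **Statistical methods:** report the aerobic-minus-Yi Jin Jing difference in AMH with its two-sided 95% confidence interval as the result for the main objective, whatever the ANOVA shows. State that P ≥ 0.05 will not be read as comparable effectiveness.
2. **Study design:** limit the superiority label to the exercise-versus-control contrasts that the Discussion hypothesises.
3. **Interpretation:** if it is to be claimed that Yi Jin Jing can replace aerobic exercise, base the claim on the interval against a margin that is justified and set before unblinding; otherwise report the comparison as inconclusive. The 6.6 pmol/L used above is an illustration, not a recommendation.

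The cost is a few sentences and one line of output, with no extra patients and no change to treatment. The downside is that the trial may have to report an inconclusive comparison where it would otherwise have reported no difference.

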### Study setting

All the medical tests will be conducted in the Yue yang Integrated Chinese and Western Medicine Hospital, Affiliated to Shanghai University of Traditional Chinese Medicine. The aerobic exercise and the *Yi Jin Jing* intervention will be conducted at Shanghai University of Sport.

### Inclusion criteria

(1). Women aged between 18 and 35 years [36, 37](2). Diagnosed with PCOS using the Rotterdam criteria, which at least two of the following are present: oligo-ovulation or anovulation, clinical and/or biochemical signs of hyperandrogenism, and polycystic ovaries as defined by ultrasonography, which is presence of 12 or more follicles in each ovary measuring 2–9 mm in diameter, and/or increased ovarian volume (> 10 mL) [38](3). BMI ≥ 23 kg/m^2^.

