### Exclusion criteria

(1). Known disorders that mimic the PCOS, such as congenital adrenal hyperplasia, androgen-secreting tumors, and Cushing’s syndrome [38](2). Cardiovascular diseases and thrombotic diseases.(3). Acute or chronic hepatitis or nephritis.(4). Taking medications known to affect ovarian function within the past 3 months.(5). Any pulmonary or musculoskeletal diseases that could be impaired by exercise.(6). Participating or having regular exercise training during the past 3 months.(7). Patients suffer from mental problems.

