#### Study measurements

Prior and post to intervention, the following will be measured. Transvaginal ultrasound scan will be performed during the early follicular phase (cycle days 3–5) to document ovary morphology, including antral follicle count and ovarian volume. Fasting blood will be taken for 2–5 days during spontaneous menstrual cycle to check biochemical profiles, including AMH, LH, FSH, T, E_2_, sex hormone binding globulin (SHBG), dehydroepiandrosterone sulfate (DHEA-S), fasting insulin (FINS), and fasting blood glucose (FBG) level. Free androgen index (FAI = T × 100/SHBG) and homeostasis model assessment of insulin resistance (HOMA-IR = FINS × FBG /22.5) will be calculated. All ultrasound and blood tests were performed at the medical laboratory of Yueyang Hospital. All participants will receive a menstrual diary to record menstrual bleedings, menstrual frequency which will be calculated by dividing the number of menstrual bleedings by 3 (ordinal variables: “0,” “1/3,” “2/3,” “1”). Anthropometric indicators including weight, height, and BMI will be measured.

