#### Outcome measurements

The primary outcome is serum AMH level. AMH is the best marker of the ovarian function; it could be noticed as a suitable hormonal marker of the ovarian follicular count and as a diagnostic marker for ovarian hyperandrogenism [44–46]. Therefore, we choose AMH as the primary outcome.

Secondary outcomes include:(1). Menstrual frequency.(2). Biochemical profile including FSH, LH, T, E_2_, SHBG, DHEA-S, FAI.(3). Antral follicle count and ovarian volume.(4). BMI(5). HOMA-IR

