#### Randomization and concealment

Eligible participants will be randomly assigned into the control group or the intervention group (aerobic exercise group or *Yi Jin Jing* group) with an allocation rate of 1:1:1. The randomization procedure will be conducted by an independent statistician using a computerized program. The allocation sequence will be stored in a sealed envelope and will not be announced until the baseline measurements have been completed.

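### Menstrual frequency is compared in all women with no stated use of baseline cycle status, which dilutes the Yi Jin Jing versus aerobic comparison (secondary outcome, low priority)

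*Protocol article*

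**What the plan says.** **Entry.** Inclusion criteria applies the Rotterdam definition: "at least two of the following are present: oligo-ovulation or anovulation, clinical and/or biochemical signs of hyperandrogenism, and polycystic ovaries". Impaired ovulation is one of three features, and any two suffice. None of the seven exclusion criteria concerns cycle regularity; the nearest is "Taking medications known to affect ovarian function within the past 3 months".

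**Scale.** Study measurements gives every participant a menstrual diary and defines "menstrual frequency which will be calculated by dividing the number of menstrual bleedings by 3", with four ordered levels: 0, 1/3, 2/3 and 1. Menstrual frequency is listed first among the secondary outcomes (Outcome measurements).

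**Analysis.** Statistical methods states: "Differences between groups of the categorical data (menstrual frequency) will be compared by Kruskal–Wallis test". A Nemenyi test follows if the result is significant. The same section says "The intention-to-treat principle will be used in the statistical analysis". It names no baseline term, stratum or subset for this outcome. Randomization and concealment describes a 1:1:1 computerised allocation and mentions no stratification.

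**Aim.** Objectives makes aerobic exercise versus Yi Jin Jing the main comparison. The Discussion hypothesises that both forms of exercise improve the menstrual pattern relative to control. Under Interventions, control women take a cyclic oral contraceptive for three cycles.

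**The concern.** A woman who already bleeds about once a month cannot gain much on a score that counts bleeds and stops at three. Whatever exercise does for women with infrequent cycles, she contributes roughly the same score in either exercise arm. Including her without using her baseline status shrinks the average difference between the arms and adds ties to the rank test.

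What is at stake is how a null result would be read. If Yi Jin Jing and aerobic exercise do not differ on menstrual frequency, the reader cannot tell whether the two act alike or whether too few of the women had a cycle problem to improve. Menstrual pattern is part of the stated hypothesis, and the comparison of the two exercise forms is the main objective.

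**Working it through.** **Plan's own figure.** There is none to reproduce. Sample size gives 25 evaluable women per group, sized on AMH. Nothing is sized on menstrual frequency. The checks below use 25 per arm.

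**Inputs not in the documents (assumptions).** These are the share q of women with regular cycles, and the size of any difference between the exercise arms. Results are shown over a range of q.

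**Step 1: dilution of the mean.** If women with regular cycles score the same in both arms and the others differ by δ on average, then

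difference in all women = (1 − q) × δ.

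Take a monthly bleeding probability of 0.40 versus 0.65 in irregular women, so δ = 0.65 − 0.40 = 0.25. At q = 20% the difference is 0.80 × 0.25 = 0.20. At q = 30% it is 0.70 × 0.25 = 0.175.

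**Step 2: power, cycle-length model.** Irregular women have a median cycle of 50 days in one exercise arm and 38 in the other (log SD 0.25 between women, 0.10 within). Regular women have cycles of 26 to 34 days in both arms. Bleeds are counted over 84 days from cycle day 5 and scored min(bleeds, 3)/3. The test is a two-group Kruskal–Wallis, two-sided 0.05.

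| Share regular | All women | Irregular at baseline only | All women, test stratified by baseline status |
|---|---|---|---|
| 0% | about 89% | same | same |
| 20% | 62% | 79% | 71% |
| 30% | 51% | 75% | 60% |

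Repeat runs agree to within about four percentage points. The restricted analysis gains power although it uses only about 25 × 0.80 = 20 or 25 × 0.70 = 17.5 women per arm. With a smaller difference (46 versus 38 days), restriction raises power from 40% to 49% at a 20% share, and from 29% to 45% at 30%.

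**Step 3: a second model.** Regular women are fixed at the top score and irregular women follow Binomial(3, p) with p = 0.40 versus 0.65.

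| Share regular | All women | Irregular only | Change scores, all women |
|---|---|---|---|
| 0% | 87% | 87% | 59% |
| 10% | 70% | 80% | 51% |
| 20% | 57% | 77% | 48% |
| 30% | 40% | 69% | 41% |
| 40% | 30% | 63% | 33% |

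The pattern is the same. Change scores do not cure the problem, because a woman at the top contributes no improvement.

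**Step 4: adding a contraceptive arm at the top score.** With bleeding probabilities of 0.45, 0.65 and 1.0 in the three arms, the three-group test on final scores is significant in essentially every run at each q from 0 to 40%. The control arm drives that result, so dilution bears on the pairwise comparison of the two exercise arms.

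**The case against.** **The contrast.** A reader might infer that case mix could produce a null result against control, since that is the comparison in the Discussion's hypothesis. The documents do not support this. Control women take a cyclic contraceptive, and their withdrawal bleeds would be expected to give scores near 1 whatever their baseline. Case mix would not cause a null there, and restricting to irregular women would not let exercise beat control. This stands, and it limits the point to Yi Jin Jing versus aerobic exercise.

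**The ceiling.** It is tempting to say that every regular-cycle woman already scores 1. Under the cycle-length model a third bleed falls inside the window only if 3L − 4 ≤ 84, that is L ≤ 29.3 days. With L uniform on 26 to 34, that is (29.3 − 26)/8, or about 41% of them; most of the rest score 2/3. The accurate statement is that they have little or no room to improve.

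**Baseline.** A reader might also infer that baseline is ignored altogether, or that no baseline diary period exists. Study design refers in general terms to comparison with baseline, and the text does not say whether the test uses final values or change. The participant timeline is a figure that is not shown. Neither inference is safe, and the point does not need them.

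**Preference or error.** Full Rotterdam entry suits a trial whose primary outcome is AMH, and the average effect in all randomised women is a legitimate intention-to-treat quantity. Both are fair, which is why the all-women result should be kept. The objection does not remove the mismatch between this scale, this population and the question about menstrual pattern.

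**Size.** The regular-cycle share and the cycle lengths are assumed, the protocol states no expected difference between the exercise arms, and the simulated two-group test is not the planned three-group test with Nemenyi follow-up. The powers are illustrations, not forecasts.

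**Conclusion.** The point holds in a limited form. The entry rule admits women with regular cycles, the score gives them little or no room to improve, and the named test makes no stated use of baseline cycle status. A difference between Yi Jin Jing and aerobic exercise on menstrual frequency is therefore diluted, in mean terms by the factor (1 − q) if regular-cycle women do not respond.

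The direction follows from the protocol's own text; the size does not. Under the assumed 50 versus 38 day difference, power falls from about 89% to 62% at a 20% regular share and 51% at 30%. Smaller effects are underpowered with or without the change.

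Priority is low. This is one secondary outcome, no power is claimed for it, and the primary AMH analysis is untouched.

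**What to change.** Add a sentence to Statistical methods, fixed before unblinded data are seen. The comparison of menstrual frequency between the two exercise arms is made in women who were oligo- or amenorrhoeic at baseline. Alternatively, use a rank test stratified by that status, which keeps every woman but recovers less power in the illustration (71% against 79% at a 20% share). Define baseline status from the cycle history already needed to judge the ovulation criterion at entry. It precedes allocation, so the comparison remains randomised.

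Report the all-women intention-to-treat result alongside, and the regular-cycle women separately as a check for worsening. The entry criteria need not change.

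The cost is a wording change, fewer women in this one secondary analysis if the subset is used, and a baseline classification that rests on recalled history.
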